### Measurements

In the recruitment visit (visit 0), all potential subjects will be advised that smokers are susceptible to COPD and that spirometry is a simple, non-invasive test that permits the detection of this disease at an early stage. They will then be informed about the study and offered the possibility of participating. Those who accept will be asked to provide their signed informed consent. Consenting participants will then be asked for all of the necessary information using a structured data collection questionnaire designed for this purpose, which will include:

• Affiliations and sociodemographic data.

• History of diseases and medications.

• History of respiratory symptoms.

• Smoking habit: current daily consumption (cigarettes/day) and accumulated consumption (packs/year averaged over years of smoking), nicotine dependence measured by the Fagerström test [26], motivation to quit smoking using the Richmond test [27] and stage of the change process according to Prochaska and DiClemente's model [28].

• Previous quit attempts: number and therapeutic resources used.

• Basic physical examination: weight, height, body mass index, blood pressure.

• Expired carbon monoxide (CO) levels determined by coximetry using the Smoke Check device (Micro Medical Limited, Rochester, Kent, England). This model detects a CO range of 0-20 particles per million (ppm) with a sensitivity of 1 ppm.

• Spirometry and a bronchodilator test, using an ultrasound pneumotacograph Datospir-600 (SIBELMED, S.A.).

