#### Sample size calculation

To achieve the study's main objective, sample size is calculated in accordance with the following parameters: identification of a difference equal to or greater than 8% between the intervention group and control group with regard to abandonment or reduction of tobacco use, a 10% abandonment or reduction in the control group, an alpha risk of 0.05, and a beta risk of 0.20 in a two-tailed contrast. Consequently, for this study it will be necessary to randomize a total of 590 subjects (295 in each group). Taking into account a withdrawal rate of 10%, the total sample size will be 649 subjects.

At each of the 12 participating centres, it should be reasonable to expect the associated researchers to include about 50 participants in this study (25 in each group).

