#### Analysis strategy

Data will be drawn from a centralized database and grouped so that those responsible for analysis will be blinded to participants' study group assignment.

The effectiveness of randomization to assess the comparability and consistency of intervention and control groups will be checked in terms of the similarity of the distribution of the variables of interest at baseline. Losses to follow-up in each group will be quantified and assessed to rule out a possible selection bias.

All analysis will be conducted on the principle of intention to treat. Losses to follow-up will be quantified in each group and assessed to determine whether any possible bias was introduced to the results. A "worst-case analysis" strategy will be used, assuming that the expected response occurred in the control group patients lost to follow-up and did not occur in the intervention group. Using this assumption, the data will be reanalyzed and the magnitude of the observed difference between the initial results and the "worst-case" estimates will be assessed. This approach is valid except in the unlikely case that losses to follow-up exceed 20%.

Standard statistical tests will be used for both quantitative and qualitative variables described (e.g. means, standard deviations, medians, proportions).

Continuous abstinence, prolonged abstinence rates, and point prevalence abstinence at 6 and 12 months after intervention will be calculated, along with Cox analysis of survival (abstinence). In cases of failure to quit, consumption data, motivation, and number of attempts to quit smoking during follow-up will be collected and compared with those who achieved a level of abstinence.

The results will be presented using both relative and absolute measures: relative risk (RR) and relative risk reduction (RRR) and absolute risk reduction (ARR) and the number needed to treat (NNT), or number of smokers who must try to quit to succeed in getting one to remain abstinent. All measures will be expressed with their respective confidence intervals (CI) of 95%.

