To assess the influence of studied parameters on the rates of abstinence and failure, logistic regression will be used, calculating odds ratios (OR) and 95% CI. As part of the statistical analysis, multiple logistic regression models will be fitted to adjust for potential confounding covariates of the primary outcome (age, sex, educational level, number of previous quit attempts, nicotine dependence, motivation to quit smoking, comorbidity, etc.) [36,37].

Statistical analysis will be performed with SPSS version 14.0. The tests will be considered significant when *P *< 0.05.

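### The covariate-adjusted primary result is planned only as an odds ratio, while the effect is to be reported as RR, RRR, ARR and NNT, so the reported measures gain nothing from the adjustment

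*Protocol article*

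**What the plan says.** All of this is in the protocol article.

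- **Reporting scale (Analysis strategy).** "The results will be presented using both relative and absolute measures: relative risk (RR"), followed by RRR, ARR and NNT, all with 95% confidence intervals.
- **Adjusted analysis (Analysis strategy, next paragraph).** Logistic regression is to yield odds ratios with 95% confidence intervals, and "multiple logistic regression models will be fitted to adjust for potential confounding covariates of the primary outcome". Seven covariates are named: age, sex, education, previous quit attempts, nicotine dependence, motivation and comorbidity. The list then ends with an open "etc".
- **Planning rates (Sample size calculation).** "a 10% abandonment or reduction in the control group" and "identification of a difference equal to or greater than 8% between the intervention group and control group", with "an alpha risk of 0.05, and a beta risk of 0.20 in a two-tailed contrast".

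The article mentions no adjusted RR, adjusted risk difference or adjusted NNT, and no step that turns the logistic model into risks. It does not say how the adjusted OR is to be read beside the RR and ARR.

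**The concern.** The trial chooses one set of scales for its effect and another for its adjusted effect, and nothing links the two. This has two consequences.

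First, adjustment for prognostic baseline variables in a randomised trial is mainly useful for precision. Here the benefit goes to a measure that is not among those chosen for reporting, and RR, ARR and NNT get none of it.

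Second, the adjusted figure invites misreading. The article calls the covariates confounders although allocation is randomised. A reader who sees an RR and then a larger adjusted number may conclude that confounding had hidden part of the effect. The Background already mixes scales: it cites an RR of 2.12 from one trial and ORs of 2.02 and 2.13 from others.

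**Working it through.** **Inputs.** Control rate 10%, difference 8 points (so 18%), two-sided alpha 0.05, power 0.80, 295 per group: all from Sample size calculation. The prognostic strength of the covariates is not given. It is assumed here as the SD, s, of their linear predictor on the log-odds scale, from 0.25 to 1.5 (c-statistic about 0.57 to 0.83).

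**1. The plan's own figure.** With pooled variance under the null and mean rate 0.14:

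n = [1.960 × √(2 × 0.14 × 0.86) + 0.8416 × √(0.10 × 0.90 + 0.18 × 0.82)]² / 0.08² = (0.9618 + 0.4102)² / 0.0064 ≈ 294.1, rounded up to 295.

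This matches the plan ("it will be necessary to randomize a total of 590 subjects (295 in each group"), so 10% against 18% is the correct reading of the design.

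**2. Effect measures at those rates.**

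- RR = 0.18/0.10 = 1.80
- ARR = 0.08, NNT = 1/0.08 = 12.5
- Crude OR = (0.18/0.82)/(0.10/0.90) = 1.976

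**3. Adjusted OR with no confounding.** Let the covariate score z be standard normal and independent of arm. For each arm j, solve for a_j so that the average of expit(a_j + s·z) over z equals p_j. The adjusted OR is exp(a_1 − a_0). For s = 1.0, a_0 = −2.564 and a_1 = −1.799, so the OR is exp(0.765) = 2.149.

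| s | Adjusted OR | Relative to crude OR | Relative to RR |
|---|---|---|---|
| 0.25 | 1.99 | +0.5% | +10% |
| 0.5 | 2.02 | +2% | +12% |
| 1.0 | 2.15 | +9% | +19% |
| 1.5 | 2.38 | +20% | +32% |

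The true RR (1.80), ARR (8 points) and NNT (12.5) are the same in every row.

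**4. Splitting the gap.** The change of scale from RR to crude OR contributes 1.98 − 1.80 = 0.18 whatever the covariates. Non-collapsibility adds about 0.04 at s = 0.5, 0.17 at s = 1.0 and 0.40 at s = 1.5.

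**5. In simulated trials** (3,000 per setting, 2 × 295). At 10% against 18%, the adjusted OR exceeded the crude RR in 98–99% of trials. It exceeded the crude OR in 60%, 68%, 83% and 93% at s = 0.25, 0.5, 1.0 and 1.5. At 10% against 10%, the adjusted OR had a median near 1.00 and exceeded the crude RR in 50–51%, so there was no systematic shift.

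**6. What misreading would cost.** If an OR of 2.15 were taken as a risk ratio on a 10% control rate, it would imply 21.5%, a difference of 11.5 points and an NNT of 1/0.115 ≈ 8.7. The true values are 8 points and 12.5.

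**7. Lower rates.** The Background cites 6.4% against 13.6% from one trial. There RR = 2.13 and crude OR = 2.30, a scale gap of 8%. The adjusted OR would be 2.35, 2.50 and 2.78 at s = 0.5, 1.0 and 1.5. The pattern is the same, with a slightly smaller scale component.

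**8. Standardising the same model.** Average the fitted risks over all participants with arm set to control and then to intervention, and compare the two averages. The median standardised RR was 1.81–1.82, the same as the median crude RR, and it exceeded the crude RR in 49–50% of trials. The variance of the risk difference and log RR fell by about 2%, 8% and 17–18% at s = 0.5, 1.0 and 1.5. In confidence-interval width that is 1 − √0.98 ≈ 1% to 1 − √0.82 ≈ 9%. These are simulation figures for a single covariate score and should be read as approximate.

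**The case against.** The strongest reply is that nothing here is invalid. A labelled conditional odds ratio beside a risk ratio is a standard analysis. The article presents the results as RR, RRR, ARR and NNT, and nowhere makes the adjusted OR the headline figure. Misreading requires someone to take an OR for an RR. Sampling error is also much larger than the shift: the log crude OR has SE √(1/29.5 + 1/265.5 + 1/53.1 + 1/241.9) = 0.246, so its 95% interval runs from about 1.22 to 3.20. And a standardisation step could sit in an analysis plan that is not shown. All of this stands, and it makes the point an improvement and not a correction of an error.

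Two further limits also stand. The 10% and 18% are stated for abandonment or reduction of tobacco use, whereas the primary outcome is CO-validated prolonged abstinence. The covariate strengths are assumed.

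Two stronger readings are tempting, and the documents do not support them.

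- A reader might infer that adjustment will by itself enlarge the effect, or that false positives become more likely. Much of the gap is the RR-to-OR scale change, which needs no adjustment. With weak covariates the adjusted OR exceeds the crude OR in only 60–68% of trials. With no true effect there is no shift.
- A reader might infer that stage of change and "current daily consumption (cigarettes/day") are left out of the model because they are collected at recruitment but not named. A list that ends openly cannot show exclusion, and settling the final list is commonly left to the analysis plan.

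The objection does not remove the mismatch in the text. The article does state a measure for the adjusted models, and it is not one of those chosen for reporting.

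**Conclusion.** The concern holds in limited form. The adjusted primary analysis is tied to a measure that is not comparable with RR, RRR, ARR and NNT, and those measures get no precision from the covariates. At the planning rates, an RR of 1.80 would stand beside an adjusted OR of about 2.02 to 2.38 with no confounding at all, for an assumed linear-predictor SD of 0.5 to 1.5. The unadjusted RR, ARR and NNT remain valid, this mechanism does not affect the type I error, and the sample size is untouched. What is lost is interpretability of the adjusted result and a precision gain of roughly 2% to 18% in variance, which could be had from a model the trial already plans to fit.

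**What to change.** Keep the planned logistic model with its named baseline covariates. From it, compute the standardised abstinence risk in each arm. Report the adjusted RR, risk difference and NNT with 95% confidence intervals (delta method or bootstrap) beside the unadjusted ones. Keep the adjusted OR as supportive, and say that it is on a different scale and should not be compared directly with the RR.

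This puts the adjusted and unadjusted results on the same scales. The cost is a few sentences in the Analysis strategy section, some extra programming, and possibly newer software than the SPSS 14.0 named there. Recruitment and sample size do not change.

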#### Ethical aspects

The protocol, informed consent form, participant information sheet and any applicable documents were submitted to an appropriate Ethics Committee (EC) and Regulatory Authority of Institute of Primary Care Research (IDIAP) Jordi Gol for written approval and the study protocol was approved by the registration number ID 4R07/040. All substantial amendments to the original approved documents will also be sent to an appropriate EC and regulatory authority for written approval.

Investigators will ensure that this study is conducted in accordance with the principles of the Declaration of Helsinki and ICH Guidelines for Good Clinical Practice, and in full conformity with relevant regulations.

All participants will be informed of the study, its objectives and activities related to their participation: number and schedule of visits, diagnostic test, results information, etc.

Written information will be given and they will be asked to sign a consent form.

Patients with any previously undiagnosed impairment will be referred to the appropriate diagnostic and therapeutic unit, which will be responsible for integrating information and providing the best diagnostic and therapeutic option.

The trial staff will ensure that participant confidentiality is maintained. Participants will be identified only by a PID number on the CRF and any electronic database. All documents will be stored securely and only accessible by trial staff and authorized personnel. The study will comply with the Data Protection Legislation requirements for anonymization of data.

## Discussion

The etiological relationship between COPD and smoking is no longer subject to discussion due to the available epidemiological, morphological and genetic evidence. There is no room for doubt that quitting smoking is the best way to reduce the risk of COPD, and is the most efficient intervention and the only effective treatment to improve survival [1]. However, smoking requires an intensive approach that is not always viable under the actual conditions of everyday clinical practice, which is often consumed with massive numbers of patient visits. Therefore, it is of fundamental importance to have evidence of ways to maximize these interventions.

The present study will evaluate, under nearly actual conditions of primary care, the efficacy of a quit-smoking strategy directed at individuals at any of the stages of change. The theoretical framework used is to provide personalized motivational information about the effects of smoking, with the goal of accelerating a change in habit. This idea is not new and was the subject of a recent Cochrane review [21]. Although certain prestigious authors and institutions [8,20] have raised questions about the usefulness of this type of strategy, recent data allow us to assume that some patients can benefit from it [22,25]. One plausible explanation of this apparent contradiction is that if an intervention is to succeed there must be some change in testing results and an adequate presentation of them [37]. If this were the case, being able to prove a change should have implications for clinical practice.

Primary care, with its population context and continuity of care throughout a patient's life, has a core role in any strategy to break a smoking habit. One of the main tasks of first-line care professionals is to increase patient motivation to quit smoking, and on many occasions it must be attempted in young, healthy smokers that have come to the doctor for some other reason. The ESPITAP study presents a pragmatic design that reflects these conditions, attempting to establish an intervention that can be easily applied in clinical practice. For that reason, it takes into account the usual attention these subjects receive and is intended to be incorporated into the daily clinical activity of the researchers.

The designed intervention is less intense than the one described in other studies that have taken a motivational approach, and this is not of marginal importance: a direct dose-response association has been demonstrated between intensity, success of the intervention, and abstinence rates [21]. Although one could then assume that another more intensive approach would be more appropriate, at the same time this would distance us from the conditions of daily practice that the study attempts to reflect.

A primary strength of the study is its rigorous methodology that involves a large number of health professionals and patients, which will strengthen the validity of the results. Although it will be difficult to control the extent to which the personal skills of the researchers might influence the success of the intervention, its format, content, and duration will be standardized in an effort to minimize this potential confounder.

## Conclusions

In conclusion, the use of spirometry as a motivational instrument for smoking cessation continues to be a controversial topic. Although the available studies seem to highlight the efficacy of this intervention, there is insufficient evidence to establish definitive conclusions about its effectiveness. The results of the present study could contribute to clarify these and other questions of practical utility for primary care professionals.
